### **8.1.1 Overview of Statistical Analysis**

Our laboratory and the HVTN Immunologic Monitoring Reference Laboratory, headed by [name] also at Duke University, has devoted considerable effort to co-developing and co-validating the immunologic assays outlined below for monitoring  $T_{Reg}$  function, antigen-specific responses in CD8+ or CD4+ T-cells, and NK cell functional activity in cancer patients. The reproducibility of these assays in our hands ensures that they can be reliably used for monitoring of changes after vaccination with and without daclizumab. Power calculations for this study are based on our primary endpoint which is functional suppressive capacity of CD4+CD25+CD127-  $T_{Regs}$ . For these calculations, we assumed that measurements made in each treatment group at a given phytohemagglutinin (PHA) level would be normally distributed with standard deviation of  $\sigma$ . Based on our experience with these assays within this patient population (Fecci, Mitchell et al. 2006), we estimate that with a sample size of 20 randomized patients we will have 80% power to detect a difference of 1.41  $\sigma$  at the 0.017 significance level (one-tailed). A 0.017 level of significance is used to adjust (Bonferroni correction) for the use of 3 non-zero PHA doses (0.1, 1, 10  $\mu$ g/well) in the proliferation assay. Thus, with only 20 patients, we will have sufficient power to detect treatment effects much more subtle than the ones observed in our pre-clinical studies (Fecci, Sweeney et al. 2006) and effects that we believe would be clinically significant. However, because the magnitude and variability of the effects of daclizumab on  $T_{Regs}$  remain unknown in humans, once human data become available from these studies, power analyses will be recalculated and patient numbers adjusted if needed. If daclizumab treatment does not significantly inhibit the functional recovery of  $T_{Regs}$  (primary endpoint), we would not be interested in the further development of this drug as

a vaccine adjuvant. Therefore, a one-sided hypothesis test is utilized. Power calculations are not provided for subsequent analyses as the number of patients in this trial will be determined by the primary endpoint, and the remainder of the analyses is exploratory and hypothesis generating only. With 10 patients in each arm, however, we will have 80% power to detect difference  $>1.325\sigma$  between groups for each assay at  $\alpha=0.05$ .

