
### **8.2.1 Statistical Analysis**

Our primary endpoint analysis will consist of a comparison of proliferative T-cell response to PHA among treatment groups (+/- daclizumab) using a generalized linear model for normal data that accounts for correlation of measurement replication across PHA doses (0, 0.1, 1, 10  $\mu\text{g/well}$ ) within subjects. This analysis determines whether the difference in treatment groups relative to proliferative response remains constant over 4 PHA doses (i.e. curves remain parallel or not). A test of interaction with 3 degrees of freedom will be used. If the curves deviate significantly from parallelism, we will conclude that the effect of treatment varies as a function of PHA dose level. Within the

context of this model, statistical contrasts will be used to assess treatment differences at specific PHA dose levels. If the test for interaction is not statistically significant, one will conclude that the treatment effect is constant over PHA dose levels. A generalized linear model without an interaction will be used to assess whether the main effect for treatment is statistically significant (i.e. treatment differences are non-zero). In this analysis and others, if assumptions required for t-tests are not satisfied, a non-parametric Wilcoxon rank sum test will be conducted at each PHA level. Significance for this and other assays will be taken at the  $\alpha=0.05$  level unless otherwise indicated. A Bonferroni correction will be used to control for the multiple comparisons.

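### Single-step Bonferroni over the three PHA doses is valid but needlessly conservative for the per-dose contrasts; Holm or a step-down max-T would be a cheap improvement, not the correction of an error

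*Protocol*

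**What the plan says.** Section 8.1.1 bases the sample size on the primary endpoint, T-reg suppressive function. It assumes that values at a given PHA level "would be normally distributed with standard deviation of" sigma, and states that "with a sample size of 20 randomized patients we will have 80% power to detect a difference of 1.41" sigma at the one-tailed 0.017 level. The reason for that level is given directly: "A 0.017 level of significance is used to adjust (Bonferroni correction) for the use of 3 non-zero PHA doses" (0.1, 1 and 10 µg/well). On sidedness it says: "Therefore, a one-sided hypothesis test is utilized".

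Section 8.2.1 describes the analysis. A linear model that "accounts for correlation of measurement replication across PHA doses" (0, 0.1, 1, 10) first tests the treatment-by-dose interaction on 3 degrees of freedom. If the curves are not parallel, contrasts at specific doses follow. If the interaction is not significant, a single main-effect test is used. If t-test assumptions fail, a Wilcoxon test is done at each PHA level. The paragraph closes with: "A Bonferroni correction will be used to control for the multiple comparisons". No value for the between-dose correlation is given.

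**The concern.** All doses are tested on the same patient's cells, and the model in 8.2.1 treats them as correlated. Single-step Bonferroni ignores that correlation. It also keeps the strictest threshold for every dose, even after one dose has been declared significant. Holm rejects everything that Bonferroni rejects, sometimes more, at the same family error and without any assumption about correlation. A step-down max-T also uses the correlation. With 10 patients per arm, dose-level effects that are really present may go unclaimed for no gain in error control.

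**Working it through.** **Inputs from the protocol (8.1.1, 8.2.1).** 10 patients per arm, normal data with common sigma, difference 1.41 sigma, three non-zero doses, one-sided testing. The per-dose level is 0.05/3 = 0.0167, rounded to 0.017, so the family level is 0.05.

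**Assumed.** Between-dose correlation rho from 0.3 to 0.9, equal for all pairs of doses.

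**Step 1: the plan's own figure.** Two-sample t-test with 10 + 10 − 2 = 18 df. Noncentrality = 1.41 × √(10/2) = 1.41 × 2.236 = 3.15. The one-sided 0.017 critical value is t = 2.29. Noncentral-t power is 79.7%, or 79.5% at exactly 0.05/3. The stated 80% reproduces.

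**Step 2: procedures compared by simulation at one-sided family level 0.05.**
- Bonferroni: every dose tested at 0.05/3.
- Holm: ordered p-values tested at 0.05/3, 0.05/2 and 0.05, stopping at the first failure.
- Step-down max-T: the same stepping, with critical values taken from the null distribution of the largest t among the doses still in play.

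| rho | True family error, Bonferroni | Per-dose power, effect at all 3 doses: Bonferroni / Holm / max-T | Effect at 2 doses: Holm / max-T | Effect at 1 dose: Holm / max-T |
|---|---|---|---|---|
| 0.3 | 4.7% | 79.5 / 88.4 / 88.7% | 83.4 / 83.9% | 79.5 / 80.4% |
| 0.5 | 4.4% | 79.5 / 87.7 / 88.4% | 83.0 / 84.4% | 79.4 / 81.2% |
| 0.7 | 3.8% | 79.5 / 86.6 / 88.4% | 82.8 / 85.6% | 79.5 / 83.2% |
| 0.9 | 3.0% | 79.5 / 84.9 / 89.2% | 82.0 / 87.6% | 79.4 / 86.6% |

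Bonferroni stays at about 79.5% per dose in every row. The step-down max-T family error is 5.0% under the global null and at most about 5.1% (simulation error) when only some doses respond.

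**Step 3: where the gain comes from.** A single-step max-T, which uses the correlation but does not step down, gives 80.3 / 81.3 / 83.3 / 86.6% at rho 0.3 / 0.5 / 0.7 / 0.9. At low to moderate correlation, therefore, nearly all of the gain comes from stepping down. Correlation contributes materially only at about 0.7 and above.

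**Step 4: power for at least one dose (effect at all three).** At rho 0.5 / 0.7 / 0.9, Bonferroni has 95.2 / 92.2 / 87.2% and max-T 95.9 / 94.1 / 92.3%. Holm equals Bonferroni here, because its first step is the Bonferroni test.

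**Step 5: the analysis sequence of 8.2.1, with PHA 0 as a fourth level.**
- *Parallel curves (1.41 sigma at all four levels).* The interaction is significant in only about 5% of trials. Overall success at rho 0.5 / 0.7 / 0.9 is 98.7 / 96.6 / 93.1% with Bonferroni and 98.7 / 96.7 / 93.3% with max-T.
- *No effect at PHA 0, 1.41 sigma at the other three.* The interaction is significant in 76 / 89 / 99 / 100% of trials at rho 0.3 / 0.5 / 0.7 / 0.9, so the contrasts are the usual route. Among those trials per-dose power is 82 / 80 / 79 / 79% with Bonferroni, 90 / 88 / 87 / 85% with Holm and 90 / 89 / 89 / 89% with max-T. Overall success at rho 0.5 / 0.7 / 0.9 moves from 95.3 / 92.2 / 86.8% to 95.8 / 94.1 / 92.4% with max-T.

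**The case against.** The strongest case against raising this is that nothing in the plan is wrong. Sections 8.1.1 and 8.2.1 agree with each other, Bonferroni controls the family error, and it delivers the stated power. That stands in full: this is lost efficiency only.

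A reader might infer that Bonferroni costs the primary analysis 8 to 9 points of power. The protocol does not support that reading, for three reasons.
- The figure needs the full 1.41 sigma effect at all three doses.
- Section 8.2.1 uses per-dose contrasts only after a significant interaction or in the Wilcoxon fallback. With parallel curves one main-effect test decides and almost nothing is lost.
- The development decision in 8.1.1 turns on whether daclizumab significantly inhibits T-reg recovery. No text requires significance at a named dose or at all doses. On the at-least-one-dose measure the gain is small with max-T and zero with Holm.

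A reader might also blame the correlation between doses. The protocol gives no value for it, and at low to moderate values stepping down explains most of the gain.

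Finally, the max-T figures use critical values from simulated null data with a known, equal correlation. A permutation version was not simulated. It would have to respect the randomisation in blocks of 3 (10.2) and the replacement of patients (5.1.1). Holm does not carry that burden.

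What survives is that the per-dose route is not a corner case. If daclizumab alters the stimulated response but not the unstimulated background, the contrasts are reached in most trials, and a uniformly better procedure is available at the same family error.

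**Conclusion.** The point holds as a cheap improvement to the per-dose contrasts. At 10 per arm and an assumed correlation of 0.3 to 0.9, per-dose power moves from about 80% as follows:
- effect at all three doses: to 85-88% with Holm, 88-89% with max-T;
- effect at two doses: to about 82-83% with Holm, 84-88% with max-T;
- effect at one dose: no gain with Holm, 1 to 7 points with max-T.

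For finding an effect at any dose, the gain is nil with Holm and about 1, 2 and 5 points with max-T at correlation 0.5, 0.7 and 0.9. These figures rest on normal data, equal correlations and a common effect of 1.41 sigma at each responding dose.

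**What to change.** In 8.2.1, replace the Bonferroni sentence by Holm for the three non-zero PHA doses, which adds no assumption. Alternatively specify a step-down max-T permutation that re-randomises arm labels under the actual allocation scheme and keeps each patient's dose values together. Keep the one-sided family level of 0.05. State that the adjustment applies to the contrasts after a significant interaction and to the Wilcoxon fallback.

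Add a matching note in 8.1.1, and keep 1.41 sigma at 0.017 there as the conservative planning figure.

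Holm costs a sentence in each section. Max-T also needs code that reproduces the block randomisation and the handling of replaced patients. With either method, simultaneous confidence limits become less simple than Bonferroni limits.

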### **8.3 TReg Counts**

TRegs levels will be determined before and after vaccination in each treatment group (+/- daclizumab), as described by us previously (Fecci, Mitchell et al. 2006), in whole blood and paired leukapheresis samples using combinations of titrated antibodies against CD3 (UCHT1), CD4 (RPA-T4), CD8 (RPA-T8), CD45RO (UCHL1), and CD25 (BD Biosciences, San Jose, California). Following incubation, Optilyse B (Immunotech, Marseille, France) are added to each sample. Cells are then re-incubated at RT for 15 minutes and diluted with distilled water. For intracellular FOXP3 staining, cells are washed and incubated for 1 hour with Fix/Perm Buffer (eBioscience, San Diego, California) and then washed and labeled with  $\alpha$ -FOXP3 (PCH101, eBioscience) for 30 minutes in the dark at 4°C in the presence of Permeabilization Buffer (eBioscience). Samples are washed and analyzed on an ARIA flow cytometer (BD Biosciences). Data analysis is performed using BD FloJo software. To further explore the potential mechanism of daclizumab in this setting, internalization of CD25 on TRegs after daclizumab will be examined using a non-overlapping antibody (MA251) that does not block the IL-2 binding site. Anti-human secondary F(ab')2 goat antibodies specific for both human IgG and IgM (Jackson ImmunoResearch, #109-116-127) that will recognize daclizumab bound to CD25 on the cell surface will also be used. This will provide data similar to that derived for our animal studies (Fecci, Sweeney et al. 2006).

#### **8.3.1 Statistical Analysis**

Assuming normal data distribution, an unpaired t-test will be used to compare treatment groups (+/- daclizumab) relative to mean TReg levels after vaccination. Because patients will be randomly assigned to each group, and both will receive equal vaccinations, differences between groups after vaccination should be attributable to daclizumab. An unpaired t-test will be used to examine baseline differences in TReg levels, however. As an exploratory analysis, a paired t-test will also be used within groups to determine differences in TReg counts before and after vaccination.

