## 8 IMMUNOLOGIC MONITORING AND STATISTICAL ANALYSIS

Immunological response evaluations for baseline values will be conducted on the pre-vaccine leukapheresis sample. An additional leukapheresis will be required for any patients who have a positive DTH skin test for PEPvIII for immunologic monitoring. Immunologic response evaluations will also be performed from peripheral blood obtained. A comparison of pre-therapy lymphocyte functions to those at intervals after each immunization and subsequently will be made. These tests may provide evidence for the inhibition of  $T_{Reg}$  function or a change in the quantity or quality of immune responses following CDX-110 immunization and will play an important role in the design of future CDX-110-based clinical trials.

Clinical and immunologic endpoints will be analyzed in all patients and statistical considerations described below are powered based on enrollment of 20 patients. However, an analysis of patients stratified at enrollment based on complete resection or residual disease will be performed for hypothesis generation on the role of tumor burden on clinical and immunologic responses to PEPvIII vaccination and daclizumab.

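### The randomised comparison of TReg counts ignores the pre-vaccination count; adjusting for it would probably gain precision at almost no cost

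*Protocol*

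**What the plan says.** **Counts.** Protocol 8.3 has TReg levels determined before and after vaccination in each arm. For the comparison, 8.3.1 says "Assuming normal data distribution, an unpaired t-test will be used to compare treatment groups (+/- daclizumab) relative to mean" TReg level after vaccination, and relies on randomisation to attribute any difference to daclizumab. It adds an unpaired t-test of baseline differences between arms and, as exploratory, paired t-tests within each arm.

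**Function (primary endpoint).** 8.2.1 uses a "generalized linear model for normal data that accounts for correlation of measurement replication across PHA doses", with a 3-degree-of-freedom treatment-by-dose interaction. It lists no baseline term and names no time point.

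**Baseline material.** Section 8 states: "Immunological response evaluations for baseline values will be conducted on the pre-vaccine leukapheresis sample". Every enrolled patient undergoes that leukapheresis (5.1.4). Section 6.2.4 also schedules monitoring blood before vaccine #1.

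**Power.** In 8.1.1, for function: "we estimate that with a sample size of 20 randomized patients we will have 80% power to detect a difference of 1.41" (in units of sigma), tested one-sided at 0.017. For the other assays: "With 10 patients in each arm, however, we will have 80% power to detect difference" above 1.325 sigma at alpha 0.05. No numerical sigma and no baseline-to-follow-up correlation is given.

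**The concern.** With 10 patients per arm, the trial is powered only for differences well above one standard deviation. A baseline count that predicts the later count would explain part of the between-patient variation, and using it as a covariate would sharpen the arm comparison without another patient or sample.

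The two uses that 8.3.1 makes of baseline do not achieve this. Under randomisation, a test of baseline differences examines a null hypothesis that is true by design, and the protocol attaches no consequence to its result. The within-arm paired tests do not compare the arms.

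The count is not peripheral: 2.2.1 puts numeric as well as functional TReg recovery in the primary objective, although 8.1.1 treats every analysis beyond the functional endpoint as exploratory.

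**Working it through.** **Inputs.** From 8.1.1: 10 per arm; 1.325 sigma at alpha 0.05 for the other assays, which include counts; 1.41 sigma at one-sided 0.017 for function. Assumed, because the protocol gives no value: correlation rho between baseline and follow-up of 0, 0.3, 0.5 and 0.7.

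**Step 1: reproduce the plan's figures.** For an unadjusted t-test with n per arm, the noncentrality is d × sqrt(n/2) on 2n − 2 = 18 degrees of freedom.
- Counts: 1.325 × sqrt(5) = 2.963; two-sided 0.05 critical value 2.101; power 80.0%. At one-sided 0.05 the power would be 88.6%, so the 1.325 figure is two-sided, which 8.1.1 does not say.
- Function: 1.41 × sqrt(5) = 3.153; one-sided 0.017 critical value 2.295; power 79.7%; detectable difference 1.414 sigma.

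Both figures are right for an unadjusted comparison of one value per patient.

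**Step 2: adjust for baseline.** The covariate reduces the residual variance to sigma² × (1 − rho²), so it removes 9%, 25% or 49% at rho 0.3, 0.5 or 0.7. It costs one degree of freedom (17 remain) and some precision through chance imbalance in the covariate, approximated here by a factor sqrt(17/18):

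noncentrality = d / sqrt(1 − rho²) × sqrt(5) × sqrt(17/18)

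**Step 3: counts at 1.325 sigma, two-sided 0.05** (critical value 2.110). The simulated power comes from 40,000 trials per setting, with chance imbalance included.

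| rho | noncentrality | power, formula | power, simulated | detectable difference (80%) |
|---|---|---|---|---|
| unadjusted | 2.963 | 80% | 80% | 1.325 sigma |
| 0 | 2.879 | 77% | 77.5% | 1.37 sigma |
| 0.3 | 3.018 | 81% | 81.0% | 1.31 sigma |
| 0.5 | 3.325 | 88% | 88.0% | 1.18 sigma |
| 0.7 | 4.032 | 97% | 96.5% | 0.98 sigma |

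At rho 0.25 the formula returns 80.0%, so break-even lies near there.

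**Step 4: function at 1.41 sigma, one-sided 0.017, single PHA dose.** Simulated power is 77.1%, 80.7%, 87.9% and 97.0% at rho 0, 0.3, 0.5 and 0.7. Detectable differences by the formula are 1.39, 1.27 and 1.04 sigma at rho 0.3, 0.5 and 0.7. These apply only if a matched baseline exists for that assay.

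**The case against.** **The gain depends on an unknown correlation, and there is reason to doubt a high one.** The flow sheet puts the baseline leukapheresis before temozolomide, so chemoradiation and a further temozolomide cycle separate it from any post-vaccination count. The draw before vaccine #1 is closer in time, but at day 21 it sits at the edge of the 14 to 21 day nadir that 3.12 reports for a five-day regimen. Neither sample is shown to predict recovery. This stands, and it makes the size of the gain conditional. The balance still favours adjustment: at worst about 3 points of power lost, against 8 to 17 gained at rho 0.5 to 0.7.

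**The existing test is sound.** This also stands. A reader might infer that the unadjusted comparison is biased, or that chance imbalance (SD of the difference in baseline means sqrt(2/10) = 0.45 sigma) is a further defect. The documents do not support that: randomisation makes the test unbiased, and its standard error and stated power already allow for such imbalance.

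**The primary endpoint.** A reader might also infer that TReg function is compared on post-treatment values alone. The text does not establish this. Section 8.2.1 names no time point, section 8 promises a general comparison of lymphocyte function before and after therapy, and covariates may be set in an analysis plan that is not at hand. Moreover, 8.2 describes the functional assay on leukapheresis samples, while a later leukapheresis is required only of patients with a positive PEPvIII skin test. Whether every randomised patient will have matched functional samples has to be settled first.

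**Conclusion.** For TReg counts the point holds. Section 8.3.1 fixes a comparison of post-vaccination levels only, although a pre-vaccination level is measured, and its two uses of baseline do not adjust the arm comparison. At 1.325 sigma, adjustment would change power from 80% to about 81%, 88% or 97% at assumed correlations of 0.3, 0.5 or 0.7, and to about 77% at 0. These figures assume normal data, a linear relation to baseline with the same slope in both arms, and 10 evaluable patients per arm.

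For function, the most that can be said is that the described model contains no baseline term. Adding one is worthwhile only where matched samples exist. The planned tests are valid and their detectable differences correct, so this is a recommended gain in precision and not a correction.

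**What to change.** **8.3.1**
- Replace the unpaired t-test with an analysis of covariance of the post-vaccination count on treatment and the patient's own baseline count.
- Name one baseline sample, the same for all patients and taken before daclizumab, for example the blood drawn before vaccine #1. Do not mix blood from after chemoradiation with leukapheresis product from before it. Name the post-vaccination sample as well.
- Keep the unadjusted t-test as a sensitivity analysis.
- Drop the baseline significance test and label the within-arm paired tests descriptive.

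**8.2.1**
- State which time point and which sample supply the functional value.
- If matched samples before and after treatment exist in all randomised patients, add the baseline response of the same assay as a covariate. Keep PHA dose and the treatment-by-dose interaction in the model.

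**Cost.** For counts, wording and one degree of freedom, with about 3 points of power at risk if baseline turns out to be uninformative. The functional model may need more than one degree of freedom if baseline slopes differ by PHA dose. No extra patients are needed, and the count analysis uses blood already scheduled.

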### **8.4 T-cell Cytokine Production**

CD4+ T-cells derived from patients in each group will be cultured in 96-well plates with 0, 5, or 10  $\mu$ g of PHA or PEPvIII or KLH. After 16 and 72 hours of culture, supernatants are harvested and processed in duplicate with a custom BioRad Bio-Plex 7-plex (IL-2, IL-4, IL-6, IL-10, IL-12 (p70), IFN- $\gamma$ , TNF- $\alpha$ ) Cytokine Reagent Kit (BioRad) to differentiate responses into TH1 and TH2 types. Briefly, supernatants are incubated with anti-cytokine conjugated beads, followed by incubation with biotinylated

detection antibody. Reaction mixture is detected with streptavidin-PE and analyzed on a Luminex 100 machine (Luminex Corporation, Austin, Texas). Unknown cytokine concentrations are calculated by BioPlex Manager software using standard curves derived from a recombinant cytokine standard. Commercial ELISAs will be used to measure IL-7, IL-15, and TGF- $\beta_{1-2}$  production as well.

